### Trial analysis

All data will be anonymised and coded so that data collection and statistical analysis is blinded to treatment allocation. The code will only be broken after the main analysis has been completed.

#### Main analysis

Statistical analysis of the primary outcome measures HKBQ and EAQ-18 will be based on an intention to treat analysis using repeated measures analysis of covariance (ANCOVA). This method adjusts each patient's follow up score for his or her baseline measurements. Data transformations such as taking logarithms may be appropriate and any missing values can be imputed using regression techniques. The analysis will be expanded to include additional prognostic variables for exploratory analysis. There are assumptions underlying the ANCOVA model which include normality of residuals, equal variances, linearity, and independence. These assumptions will be tested, in particular the homogeneity of regression assumptions.

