### Randomisation

Randomisation will balance the two groups by site of pain, age, gender and duration of symptoms. As all patients are consented prior to randomisation, this will use an optimal allocation approach proposed by Raab [38] and algorithms developed by Carter [39]. Patients will be recruited from each practice and then randomised as a block. Within the block all potential allocations to two groups will be calculated and their balance statistic calculated. The 1% with the nearest optimal balance will be passed to an independent statistician who will randomly select the allocation for use and randomly allocate groups. The balance calculations for subsequent blocks will incorporate the degree of balance for the chosen allocation to ensure close to optimal balance across groups.

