### Sample size

In order to detect a moderate to large effect size of 0.55 in change in illness and treatment beliefs, with 80% power and a significance level of 5%, a sample size of 100 will be needed. We anticipate that 30% of those invited will agree to participate, and 80% of those recruited will return their final questionnaires; so that 400 patients will need to be sent letters inviting them to participate, 120 will be recruited, and 100 will return final questionnaires.

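### The regression-imputation sentence for HKBQ and EAQ-18 allows single imputation and does not require imputation uncertainty to reach the standard errors

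*Protocol article*

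**What the plan says.** The Main analysis section of the protocol article analyses HKBQ and EAQ-18 by intention to treat with repeated measures ANCOVA, and explains that "This method adjusts each patient's follow up score for his or her baseline measurements". On missing data it says only that "any missing values can be imputed using regression techniques". It does not say whether imputation is single or multiple, which predictors are used, whether arm is one of them, or how the standard errors are obtained.

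The Sample size section gives the expected loss in two ways. The counts are "120 will be recruited, and 100 will return final questionnaires", which leaves 20 of 120 (16.7%) missing. The percentage is "80% of those recruited will return their final questionnaires", which leaves 24 of 120 (20%) missing. Questionnaires are posted at baseline, one month and three months (Postal questionnaires).

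The Analysis of secondary outcomes section applies the same type of model to WOMAC, IPAQ and the other scales, and passes the WOMAC and IPAQ effect sizes to the phase III sample size calculation. It does not mention imputation.

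**The concern.** The article is not silent here: it names a remedy for missing primary outcomes. Classical repeated measures ANCOVA drops anyone who lacks a visit, so under intention to treat the imputation step is the likely way of keeping all 120 participants in the analysis.

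Single regression imputation puts each missing score on (or randomly around) a fitted line and then counts it as one more observation. What follows depends on the imputation model:

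- With arm as a predictor, the imputed values repeat the arm difference seen in the responders and add no information. The effect estimate is unchanged, but its standard error is too small.
- Without arm, the imputed values carry no arm difference, so the estimated effect is pulled towards zero.

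At stake are the p-values, confidence intervals and effect estimates for the two primary outcomes, in a trial meant both to test effectiveness on beliefs and to inform a larger trial.

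**Working it through.** **Inputs from the article.** 120 recruited; 20 or 24 without a final questionnaire; significance level 5%; standardised effect 0.55; two groups; ANCOVA adjusted for baseline.

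**Assumptions, not in the article.** Two-sided test; 60 per arm; values missing completely at random; every non-returner imputed; baseline-to-follow-up correlation 0.3, 0.5 or 0.7; SD = 1.

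**The plan's own figures.** For an effect of 0.55 with 80% power, n per arm = 2(1.96 + 0.84)²/0.55² = 51.9, so 52 per arm and 104 in total (106 by the t-test), against the stated 100. With 50 per arm the power is 78.5%. Also 100/120 = 83.3%, whereas 80% of 120 is 96. The two retention figures disagree, so both losses are carried below. The article states no error rate under imputation beyond the nominal 5%.

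**Arm in the imputation model, formula.** Let n be the number observed and N = 120. The estimate equals the complete-case estimate, with variance 4σ²/n. The residual sum of squares is unchanged by values lying on the fitted line, but it is divided by N − 3 and the variance uses N. The naive variance is therefore σ² × (n − 3)/(N − 3) × 4/N, and

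SE ratio (naive/true) = √[(n − 3)/(N − 3) × n/N].

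- 20 missing: √(97/117 × 100/120) = 0.83. The critical value 1.98 acts as 1.98 × 0.83 = 1.65, giving a type I error of about 10%.
- 24 missing: √(93/117 × 96/120) = 0.80. The critical value acts as 1.58, giving about 11-12%.

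**Arm left out, formula.** The estimate is n/N times the complete-case estimate: 0.55 × 100/120 = 0.46, or 0.55 × 96/120 = 0.44. Ignoring the small degrees-of-freedom terms, its true variance is (n/N)² × 4σ²/n = 4σ²n/N². The naive variance is σ²(n/N) × 4/N, which is the same. The test therefore keeps its level while the effect is diluted.

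**Simulation under the null.** 12,000 trials per setting (4,000 for multiple imputation with 20 imputations and arm in the model). Ranges are over the three correlations.

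| Type I error, single follow-up | 20 missing | 24 missing |
|---|---|---|
| Complete-case ANCOVA | 4.8-5.2% | 4.9-5.3% |
| Single, on the line, with arm | 10.2-10.9% | 11.8-12.1% |
| Single, with random noise, with arm | 9.2-9.5% | 10.4-10.8% |
| Single, on the line, without arm | 4.8-5.2% | 5.0-5.3% |
| Multiple imputation, Rubin's rules | 4.7-5.2% | 4.5-5.6% |

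The simulation standard error at 5% is √(0.05 × 0.95/12,000) = 0.2 points, or 0.3 points with 4,000 trials.

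**Both visits.** The planned analysis uses two follow-ups, so the check was repeated with baseline correlation 0.5, correlation 0.6 between follow-ups, and one-month loss assumed to be half the three-month loss (10 or 12). For single imputation on the line with arm, the type I error for the average over both visits is 8.1% (20 missing at three months) and 9.0% (24 missing). For the three-month effect alone it is 9.6% and 10.7%. Without arm it is 4.6-5.1%.

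**SD of the filled-in data, for any outcome treated this way.** With missing share f and correlation ρ, the within-arm variance becomes about (1 − f) + fρ² = 1 − f(1 − ρ²). The shortfall runs from 0.167 × 0.51 = 8.5% to 0.20 × 0.91 = 18.2%. A sample size scales with the variance, so it would fall short by the same share.

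**The case against.** The strongest reply is that the article does not prescribe the method examined above. A reader might infer that the plan commits to single imputation with filled-in values analysed as observed, and that the false-positive rate is therefore doubled. The text does not support that. The wording is permissive, neither single imputation nor treatment as observed data is stated, and regression techniques can include multiple imputation, which holds about 5%. The article also condenses a fuller plan, where predictors and pooling rules commonly sit. All of this stands, and it makes the finding conditional. It does not remove it: the article chooses a class of method for its primary outcomes, and on the plain reading that class includes one that gives wrong results.

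Other limits also stand:

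- The two harms come from different imputation models and cannot occur together.
- The 10-12% applies to one follow-up; the average over both visits gives 8-9%.
- The article does not say whether missing values means unreturned questionnaires, skipped items or both. If only skipped items were imputed, the effect would be smaller.
- Power is based on 100 returned questionnaires, so the sample size does not rely on imputed cases.
- A reader might infer that the effect sizes sent to phase III will be distorted. The article does not say that WOMAC or IPAQ values would be imputed, so this is only a possibility.

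**Conclusion.** The concern holds in a conditional form. The imputation sentence permits single regression imputation of HKBQ and EAQ-18 and does not require imputation uncertainty to be carried into the standard errors.

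On that reading, with 20 to 24 of 120 imputed, one of two results follows. With arm in the imputation model, the type I error is about 10-12% at a single follow-up and about 8-9% for the two-visit average. With arm left out, the level stays near 5%, but 0.55 becomes about 0.44-0.46 at a single follow-up. Adding random noise to a single imputation does not cure the first problem.

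The sizes rest on a two-sided test, equal allocation, values missing completely at random, every non-returner imputed and, for the two-visit figure, one-month loss at half the three-month loss. Severity: should-fix. The consequence for the primary analysis can be material, but it depends on a reading that the text allows rather than states.

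**What to change.** Replace the imputation sentence with one of the following.

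1. Preferred: analyse all available one- and three-month scores with a likelihood-based repeated measures model containing baseline score, arm, time and arm-by-time, with no single imputation.
2. If values are imputed: use multiple imputation with arm, baseline score, the other follow-up score and the balancing variables (site of pain, age, gender, duration of symptoms) as predictors, combined by Rubin's rules.

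Arm can enter under its code, so blinded analysis is not affected. If missing WOMAC or IPAQ values are also to be imputed, say so and use the same approach, so that the effect sizes and SDs passed to phase III are not distorted.

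The cost is a change of wording and standard software, with no new data. Confidence intervals will be slightly wider than under single imputation, and correct.

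### The primary ANCOVA as written omits the variables that restrict the allocation (pain site, age, gender, symptom duration, practice), so its standard error is too large to the extent that they predict outcome

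*Protocol article*

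**What the plan says.** Under Randomisation, the protocol article states: "Randomisation will balance the two groups by site of pain, age, gender and duration of symptoms". Practices are the blocks: "Patients will be recruited from each practice and then randomised as a block". The restriction is tight: "The 1% with the nearest optimal balance will be passed to an independent statistician who will randomly select the allocation for use". Balance accumulates over practices: "The balance calculations for subsequent blocks will incorporate the degree of balance for the chosen allocation". Under Timing of randomisation, the information used comes from the baseline questionnaire, so it is in hand before allocation.

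Under Main analysis, HKBQ and EAQ-18 are analysed by intention to treat with repeated measures ANCOVA, described thus: "This method adjusts each patient's follow up score for his or her baseline measurements". The only mention of other covariates is "The analysis will be expanded to include additional prognostic variables for exploratory analysis". Analysis of secondary outcomes applies the same type of model to IPAQ, TSK, WOMAC, SF-12 and EQ-5D. Neither section names the balancing variables or practice as covariates.

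**The concern.** Restricting allocation to well-balanced candidates removes most of the chance difference between arms on the balanced variables. The treatment estimate therefore varies less over the permitted allocations than it would under simple randomisation. A model without those variables does not know this. Their contribution to outcome stays in the residual variance, and the standard error is computed as if the arms could still differ on them by chance. The reported interval is then too wide and the test rejects less often than 5% under the null.

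What is at stake is reported precision and power in a trial of about 100 analysed patients. The design takes trouble to secure balance, and the analysis as described does not claim the benefit. The effect sizes for WOMAC and IPAQ are also meant to inform the phase III sample size, so the width of their intervals has a use beyond this trial.

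**Working it through.** **Inputs from the article.** Sample size gives a "moderate to large effect size of 0.55 in change in illness and treatment beliefs", 80% power, 5% significance and 100 analysed out of 120 recruited. There are four practices. Assumed here: a two-sided test, 50 per arm, and 0.55 expressed on the residual SD after the baseline score. The article does not give R², the share of that residual variance explained by the allocation variables, so a range is used.

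**The plan's own figure.** n per arm = 2 × (1.960 + 0.842)² / 0.55² = 51.9, so 52 per arm and 104 in total, against the stated 100. With 50 per arm, SE = √(1/50 + 1/50) = 0.200, and power = Φ(0.55/0.200 − 1.960) = Φ(0.79) = 78.5%. The stated 100 is a slight rounding down and does not affect this point.

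**Formulas, for exact balance.** Let s = √(1 − R²), the ratio of the true SE to the unadjusted model's SE.

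- Excess of the model SE: 1/s − 1
- True two-sided type I error: 2 × [1 − Φ(1.960/s)]
- Power, unadjusted: Φ((2.75 − 1.960)/s)
- Power, adjusted: Φ(2.75/s − 1.960), where 2.75 = 0.55/0.200

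For example, at R² = 0.20, s = 0.894. The excess is 1/0.894 − 1 = 11.8%, unadjusted power is Φ(0.79/0.894) = 81.1%, and adjusted power is Φ(2.75/0.894 − 1.960) = 86.7%.

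| Assumed R² | Model SE too large by | Type I error, unadjusted | Power, unadjusted | Power, adjusted |
|---|---|---|---|---|
| 0 | 0% | 0.050 | 78.5% | 78.5% |
| 0.05 | 2.6% | 0.044 | 79.1% | 80.6% |
| 0.10 | 5.4% | 0.039 | 79.8% | 82.6% |
| 0.20 | 11.8% | 0.028 | 81.1% | 86.7% |
| 0.30 | 19.5% | 0.019 | 82.7% | 90.8% |

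**Check by simulation.** The best-1% rule balances closely but not exactly, so it was simulated: four practices of 25, the best 1% of 1,000 sampled candidates per practice, balance carried forward, 3,000 runs per R², and one follow-up score. The adjusted model includes the four variables and practice.

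| Assumed R² | Unadjusted: model SE / empirical SE | Unadjusted: type I error, power | Adjusted: model SE / empirical SE | Adjusted: type I error, power |
|---|---|---|---|---|
| 0 | 0.200 / 0.200 | 0.050, 77.3% | 0.201 / 0.201 | 0.051, 76.8% |
| 0.05 | 0.200 / 0.196 | 0.043, 78.0% | 0.195 / 0.196 | 0.046, 79.6% |
| 0.10 | 0.200 / 0.191 | 0.042, 77.6% | 0.190 / 0.191 | 0.055, 80.6% |
| 0.20 | 0.200 / 0.183 | 0.032, 79.4% | 0.179 / 0.183 | 0.053, 85.3% |
| 0.30 | 0.201 / 0.171 | 0.024, 80.7% | 0.168 / 0.169 | 0.051, 90.1% |

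The simulated excess is 0.200/0.196 − 1 = 2.0% at R² = 0.05, 0.200/0.191 − 1 = 4.7% at 0.10, and 0.200/0.183 − 1 = 9.3% at 0.20. This is slightly below the formula, as expected with near-exact balance. A second simulation, with 30 recruited per practice and 17% dropout, gave a similar picture at R² = 0.20: unadjusted type I error 0.033, and power rising from 80% to 86% with adjustment. Loss to follow-up therefore does not undo the effect.

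**The case against.** **The covariate list may be wider than it looks.** The article never says that the baseline score is the sole covariate. It refers to baseline measurements in the plural, does not name the additional prognostic variables, and is a condensed account. That is fair as far as it goes. But the sentence concerns adjusting a follow-up score for its baseline, and the next mention of covariates calls them exploratory. Nothing in the text suggests that the allocation variables are already in the model and that the exploratory ones lie beyond them. If that was meant, the wording still needs to say so.

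**The size is not known.** This stands. A reader might infer that the standard errors are simply too large. The article gives no R², and at R² = 0 the two models are equivalent. The large figures come only from the top of an assumed range.

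**The consequence is mild.** This also stands. A reader might infer bias or false positives; neither follows, because the error is conservative. Nor is the precision of the allocation lost from the estimate: the unadjusted empirical SE falls from 0.200 to 0.183 at R² = 0.20. What is lost is the ability to report that precision and test with it.

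**Power may be better than shown.** The article sets 0.55 on change, while the residual variance under ANCOVA is no larger than that of change. Power under the planned model could therefore exceed these figures, so the calculation does not show that the trial falls short of 80%.

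**Practice.** The article targets cumulative balance and does not state equal arms within each practice. That practice variation is removed from the comparison is an inference from blocking.

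**Conclusion.** The point holds in conditional form. The allocation is tightly restricted on four named variables, with practices as blocks, and the primary model as written does not include them. If they predict HKBQ or EAQ-18 beyond the baseline score, the model-based standard error is too large and the test is conservative. For an R² of 0.05 to 0.20 the excess is roughly 2% to 12%, and the power forgone roughly 1.5 to 6 percentage points.

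These figures rest on assumed R² values, 50 per arm, a two-sided 5% test, one standardised follow-up score rather than the two planned time points, and 0.55 on the residual SD. The direction does not depend on the exact values; the size does. No separate calculation was made for the secondary outcomes, so including them in the fix is a matter of consistency. This is a worthwhile correction, not a threat to the trial's validity.

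**What to change.** In Main analysis, state that the ANCOVA models for HKBQ and EAQ-18 include pain site, age, gender, symptom duration and practice as prespecified covariates beside the baseline score. Make the same change in Analysis of secondary outcomes. Report the baseline-score-only model as a sensitivity analysis, and keep the exploratory label for variables that play no part in the allocation.

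The cost is wording and about seven degrees of freedom out of roughly 100: four if each balancing variable takes one, plus three for four practices. A pain-site variable with more than two categories would take a little more. No new data are needed. If the variables turn out to explain nothing, the loss is negligible: the simulated SE is 0.201 against 0.200.

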#### Analysis of secondary outcomes

Statistical analysis of the secondary outcome measures IPAQ, TSK, WOMAC, SF-12, EQ-5D will also be based on an intention to treat analysis using repeated measures ANCOVA. The effect size of WOMAC and IPAQ will inform the sample size calculation for a future phase III trial.

#### Assessment of feasibility of the phase III trial

Feasibility will be assessed by process measures of: the numbers of eligible participants identified, contacted and recruited with reasons for non-inclusion; the numbers of participants retained by the trial at one month and three months.

#### Psychometric testing of the modified outcome measures

The modified HKBQ and the modified EAQ-18 will be tested concurrently within the trial using criteria developed by Streiner and Norman [40].

Reliability will be measured in terms of internal consistency and test-retest reliability. Internal consistency will be measured using Cronbach's alpha on the baseline scores. This will be considered too low if below 0.7 and too high if greater than 0.9 to avoid item redundancy. Test-retest reliability will be assessed by comparing the baseline questionnaire with the retest questionnaires at one and three months. Transition questions to assess change in illness or treatment beliefs will be used with each follow up questionnaire. Those reporting that their beliefs were unchanged will be included in a test-retest analysis by calculating an intra-class correlation co-efficient (ICC) [41], and by calculating limits of agreement according to the method of Bland and Altman [42].

Construct validity will be assessed by comparing baseline with repeat questionnaires, if the transition questions indicate that beliefs have changed. Changes in beliefs will also be compared with changes in behaviour as measured by the physical activity questionnaire, and with changes in health status as measured by WOMAC and SF-12.

Responsiveness will be measured using the modified standardised response mean. The numerator of this statistic will be change in score when the transition question reports that beliefs have changed; the denominator will be the standard deviation of the change score when beliefs are unchanged [43].

### Cost effectiveness analysis

Mean health care costs of service use by patients in the control and intervention groups will be calculated and compared using non-parametric bootstrapping. Health economic analysis will initially involve a cost-consequences analysis of all the costs and outcomes collected [35]. We will calculate a bootstrapped incremental cost utility ratio (ICUR) point estimate of the cost per Quality Adjusted Life Year (QALY) to be gained from this intervention as compared with the control, using EQ-5D as a source of utility weights [33]. We will use bootstrapping to generate a cost-utility acceptability curve to inform policy makers of the probability that the intervention is cost-effective [35,44]. We will compare our estimate of the cost per QALY with the ceiling of £30,000 used by NICE. Given the relatively small sample size for this Phase II RCT, the findings will give a useful indication of the approximate size of the cost per QALY ratio for this intervention. It will inform the sample size calculation for a sufficiently powered future definitive RCT and concurrent economic evaluation. This trial platform offers an opportunity to compare EQ-5D values with SF-12 values and the other outcome measures of the trial in order to make some assessment of its sensitivity and appropriateness for use in a full trial [45].

### Ethical approval

Ethical approval was obtained from the North Wales East Research Ethics Committee [REC reference 09/WNo03/5].

## Discussion

A number of issues arise from our use of this phase II trial to not only test the processes for a larger definitive trial, but also to assess effectiveness in terms of intermediate outcomes and concurrently validate the primary outcome measures.

### Testing the effectiveness of intermediate outcomes

From our theoretical framework for developing 'The Hip and Knee Book' we have presumed that people with OA knee or hip have unhelpful beliefs and fears which are responsible for increasing their level of disability. We hypothesise that reading the new booklet, and not the control booklet, will alter their illness and exercise-related beliefs (measured by HKBQ and EAQ-18 respectively), reduce their fear of movement (measured by TSK), change their behaviour to increase their physical activity (measured by IPAQ), which will in turn reduce pain, stiffness and disability (measured by the condition-specific outcome measure WOMAC) and lead to improved general health status (measured by SF-12) and health utility (measured by EQ-5D). Outcomes measuring links higher up this theoretical chain are likely to be more responsive than links further down. Definitive or phase III trials need primary outcomes measuring health status or health utility, which are 'downstream', less responsive and require larger sample sizes. For this smaller phase II trial we have presumed that their will be a larger change in more 'upstream' intermediate outcomes such as illness and treatment-related beliefs. The position of these outcome measures in this theoretical chain can be debated. It may be that before illness and treatment beliefs change participants' fear of movement must be addressed. Alternatively change in participants' views about the prognosis of their arthritic condition, and the benefit of exercise, may lead to a reduction in the fear of movement. Self-efficacy is also important in changing behaviour such as exercise. Although we did not include a separate measure of self-efficacy so as not to over-burden our participants, some of the individual items in the EAQ-18 outcome measure do address this.

